### Sensor-augmented pump (SAP) therapy

Participants randomised to SAP therapy will receive training on the effective use of real-time CGM for optimisation of insulin therapy. During SAP therapy, participants will enter information related to carbohydrate content of the meals and premeal capillary glucose values into the bolus wizard of the insulin pump. Participants will be instructed not to activate threshold suspend (low-glucose or predictive low-glucose suspend features). Hypoglycaemia and hyperglycaemia alarms can be activated and personalised as per participants’ requirements.

### Contact during 3-month home study period

Participants will have identical planned contact visits with the study team during the two study periods. The first planned contact will occur 24–48 hours once study period has begun. During the first 2 weeks of the study period, participants will be contacted weekly. Thereafter, participants will be contacted monthly. Participants will be free to optimise their treatment independently.

### Devices download

Participants will be instructed to download insulin delivery and glucose data weekly from the insulin pump and blood glucose metre using the Medtronic Carelink Clinical download facility.

### Closed-loop system and low glucose suspend feature

The FlorenceM closed-loop system (figure 2, University of Cambridge, Cambridge, UK) comprises a model predictive control algorithm residing on an Android smartphone that communicates wirelessly with the insulin pump using a proprietary enclosure.

**Figure 2 F2:**
[figure not shown]
Closed-loop system prototype. (A) Components of the FlorenceM closed-loop system consist of a continuous glucose monitoring (CGM) transmitter with Enlite 3 sensor, an insulin pump (modified 640G pump) integrated with the CGM receiver and a mobile phone running the control algorithm. (B) A photo of a participant (obtained with consent) using the closed-loop system.

Every 10 min, the system calculates a new temporary basal insulin infusion rate, which is automatically sent to the study insulin pump. Calculations use a compartment model of glucose kinetics describing the effect of rapid-acting insulin analogues and the carbohydrate content of meals on glucose levels.^20^ The control algorithm will be initialised using preprogrammed basal insulin delivery downloaded from the study pump. In addition, information about participants’ weight and total daily insulin dose will be entered at setup. During closed-loop operation, the algorithm adapts itself to a particular participant. The treat-to-target control algorithm aims to achieve a default glucose level of around 5.8 mmol/L and adjusts the actual level depending on fasting versus postprandial status and the accuracy of model-based glucose predictions. Sensor glucose, insulin delivery, carbohydrate content and other information can be visualised by the participants on the smartphone device.

No remote monitoring is instigated. For data collection purposes, the control algorithm device uploads data on a server when the system is charging and connected to Wi-Fi.

The pump comprises a CGM receiver and provides hypoglycaemia and hyperglycaemia alarms. Hypoglycaemia and hyperglycaemia alarms can be activated and personalised as per participants’ requirements. The insulin pump provides standard insulin pump alarms, and the smartphone alerts the user about aspects related to closed-loop operations (closed-loop started, stopped or terminated).

### Safety precautions during closed-loop

Participants will be trained to perform calibration checks before breakfast and evening meals. If sensor glucose is above finger-stick glucose by more than 3.0 mmol/L, the glucose sensor will be recalibrated. These instructions resulted from an in-silico simulation of hypoglycaemia and hyperglycaemia risk using the validated Cambridge simulator.^21^

If sensor glucose becomes unavailable, preprogrammed insulin delivery will be automatically started within 30 min. This limits the risk of insulin underdelivery and overdelivery. Safety rules limit maximum insulin infusion and suspend insulin delivery at sensor glucose at or less than 4.3 mmol/L or when sensor glucose is rapidly decreasing.

In the event of closed-loop becoming unavailable due to loss of sensor glucose input or other system failures, insulin delivery will be suspended by the low glucose suspend feature set on the insulin pump, provided sensor glucose is available. Resumption of insulin delivery will be in accordance of the low glucose suspend feature implemented on 640G pump.

### Participant withdrawal criteria

The following prerandomisation withdrawal criteria will apply:Participant is unable to demonstrate safe use of study insulin pump and/or CGM during run-in period as judged by the investigatorParticipant fails to demonstrate compliance with study insulin pump and/or CGM during run-in period.

The following prerandomisation and postrandomisation withdrawal criteria will apply:Participants may terminate participation in the study at any time without necessarily giving a reason and without any personal disadvantageSignificant protocol violation or non-complianceAny severe hypoglycaemia event related to use of the closed-loop systemThree severe hypoglycaemia events unrelated to the use of the closed-loop systemDiabetic ketoacidosis (DKA) unrelated to infusion site failure and related to the use of the closed-loop systemDecision by the investigator or the sponsor that termination is in the participant’s best medical interestParticipant becomes pregnant during the study periodAllergic reaction to insulinAllergic reaction to adhesive surface of infusion set or CGM sensorIf patient continues to use pump suspend feature in the control group despite advice to the contrary.

Withdrawn participants due to reasons 4–12 will be invited to provide blood sample at the end of the planned study intervention for the assessment of HbA1c.

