### HbA1c samples

Blood samples for the measurement of HbA1c levels will be taken at three different time points. At screening, HbA1c will be measured locally. HbA1c at the beginning and end of study intervention will be taken and measured at a central laboratory (University of Minnesota, Minneapolis, USA) using an International Federation of Clinical Chemistry and Laboratory Medicine aligned method.

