### Statistical analysis

All analysis will be conducted on an intention-to-treat basis. Data from all randomised participants with or without protocol violation including dropouts and withdrawals will be included in the analysis. Data will not be truncated due to protocol deviations.

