#### Secondary endpoints

The following outcomes on the two treatment arms will be compared:HbA1c at 12 weeksTime spent below target glucose (3.9 mmol/L) (70 mg/dL)Time spent above target glucose (10.0 mmol/L) (180 mg/dL)Average, SD and coefficient of variation of glucose levelsTime with glucose levels <3.5 mmol/L (63 mg/dL) and <2.8 mmol/L (50 mg/dL)Time with glucose levels in the significant hyperglycaemia (glucose levels >16.7 mmol/L) (300 mg/dL)Total, basal and bolus insulin dose (units/kg of body weight)Area under the curve of glucose below 3.5 mmol/L (63 mg/dL)Number of pump suspend events (applicable to intervention arm)Change in body weight from screening to end of study.

Glycaemic metrics will be based on sensor glucose levels collected during the 12-week intervention period. Similar linear models as the primary outcome will be used to compare the between-treatment difference. For those metrics that have highly skewed distribution, a ranked normal score transformation of outcome data will be applied in the regression model. p Value <0.05 will be used to declare statistical significance for selected secondary outcomes (HbA1c, glucose CV, % time below 3.9 mmol/L, % time above 10.0 mmol/L, total daily insulin and change in body weight). For other outcomes, to reduce the inflation of type I error caused by multiple comparisons, p value <0.01 will be used to define statistical significance.

A subset of sensor glucose and insulin metrics will also be tabulated separately for daytime period (08:00–00:00) and night-time period (00:00–08:00).Percent time with glucose in target range of 3.9–10.0 mmol/L (70–180 mg/dL)Mean glucoseGlucose variability as measured by SDPercent time with glucose level <3.5 mmol/L (63 mg/dL)Amount of delivered insulin.

Trends in sensor glucose data collected within intervention arms will be evaluated on a 4-weekly basis.

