### Power calculation

On the basis of our previous day-and-night closed-loop studies^10 23^ and a conservative estimate of 10%points improvement in time when glucose is in target glucose range with an SD of 14.5% points, 76 subjects are required to achieve 85% power and an alpha level of 0.05 (two tailed). A total of 84 are planned to be randomised to allow for dropouts. It is expected that 95 or more subjects will be recruited; recruitment will continue until it is anticipated that a sufficient number have been enrolled to meet the randomisation goal. Randomisation target may be exceeded since all of the subjects who have initiated the run-in phase will be permitted to continue into the intervention.

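### The end-of-intervention HbA1c invitation omits participants who withdraw voluntarily, so an outcome tested at p<0.05 has no planned collection for them

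*Protocol article*

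**What the plan says.** The section on participant withdrawal criteria has two lists. The first opens with "The following prerandomisation withdrawal criteria will apply" and has two items. The second, for withdrawal before or after randomisation, has ten; it begins with the participant's free choice to leave and ends with continued use of the suspend feature in the control group. The section closes: "Withdrawn participants due to reasons 4–12 will be invited to provide blood sample at the end of the planned study intervention", for assessment of HbA1c.

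The section on HbA1c samples plans three measurements. Screening is local; for the other two, "HbA1c at the beginning and end of study intervention will be taken and measured at a central laboratory". Tables 2 and 3 place those two at Visit 5 and Visit 11, with none in between.

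The statistical analysis section says: "Data from all randomised participants with or without protocol violation including dropouts and withdrawals will be included in the analysis". The secondary endpoints section lists HbA1c at 12 weeks first and says "p Value <0.05 will be used to declare statistical significance for selected secondary outcomes (HbA1c, glucose CV" and four others).

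**The concern.** The rule asks for a final HbA1c from people withdrawn for every reason that can apply after randomisation except their own choice. A participant who stops using the device and is withdrawn for non-compliance is invited; one who says openly that they wish to stop is not. Whether follow-up is sought then depends on how the departure is classified.

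With no HbA1c sample between Visit 5 and Visit 11, a voluntary leaver has no planned post-treatment value at all. This differs from the sensor outcomes, where readings up to the point of leaving can still be used. Participants know their allocation, so the decision to leave may be related to arm and to glycaemic experience. At stake is how completely the HbA1c comparison covers those randomised.

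**Working it through.** **1. Which reason is left out.** The text at hand does not show item numbers, so the items are counted in printed order.

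- Before randomisation only: 2 items, reasons 1–2.
- Before or after randomisation: 10 items, reasons 3–12.
- Total: 2 + 10 = 12, which matches the upper end of the range 4–12.
- Reason 3 is the first item of the second list, voluntary termination.

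Reasons 1–2 cannot apply after randomisation, so reason 3 is the only post-randomisation reason not invited.

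**2. Whether another section fills the gap.** The HbA1c samples section and Tables 2 and 3 give screening, Visit 5 and Visit 11 only. None provides a sample for someone who has left voluntarily.

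**3. The plan's own sample-size figure.** The power calculation assumes "10%points improvement in time when glucose is in target glucose range with an SD of 14.5% points" and concludes that "76 subjects are required to achieve 85% power and an alpha level of 0.05 (two tailed"). With 1:1 allocation (assumed) and the normal approximation:

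n per arm = 2 × (1.960 + 1.036)² × 14.5² / 10² = 37.8, rounded up to 38; total 76.

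The figure reproduces. The article then says: "A total of 84 are planned to be randomised to allow for dropouts". The allowance is 84 − 76 = 8 participants, or 8/84 = 9.5%, and covers dropouts of any kind. These figures concern the primary endpoint; they serve here only to bound how many might leave.

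**4. Illustrative effect on HbA1c.** The article gives no HbA1c SD, target effect or expected number of voluntary leavers, so what follows rests on assumptions. Take 42 per arm, an analysis of observed values only, and the same gap g in both arms between leavers' and completers' mean HbA1c. With m1 and m2 unmeasured leavers:

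bias in the between-arm difference = (m1 − m2)/42 × g

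| Leavers by arm | g = 0.3 | g = 0.5 | g = 1.0 |
|---|---|---|---|
| 4 and 4 | 0 | 0 | 0 |
| 4 and 0 | 0.029 | 0.048 | 0.095 |
| 6 and 2 | 0.029 | 0.048 | 0.095 |
| 8 and 0 | 0.057 | 0.095 | 0.190 |

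Values are HbA1c percentage points. The rows 4 and 0 and 6 and 2 agree because the difference in leavers is 4 in both. The last row needs the whole dropout allowance to be voluntary and in one arm, so it is an extreme case. The planned model adjusts for baseline, so the relevant gap is what remains after that adjustment and may be smaller than g.

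**The case against.** The strongest counter-argument is that reason 3 is leaving the study, not stopping the device. Not approaching such people again may be a deliberate and defensible line. Participants who merely stop closed loop need not be withdrawn: they are trained to switch back to usual pump therapy, and the per-protocol section presupposes that some randomised participants fall below 80% closed-loop use. They would reach Visit 11 as planned. This narrows the affected group to those who actually leave. It does not defeat an invitation that can be refused, and the article does not separate leaving from declining one last blood sample.

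A second objection is that missing data belong to the separate analysis plan. That is right for the handling of missing values, but an analysis plan cannot recover samples that were never requested.

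Several stronger readings do not stand:

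- A reader might infer that the clause contradicts the intention-to-treat statement. That statement commits to including the data from everyone randomised; it does not promise that every outcome is obtained from everyone.
- A reader might infer that the missing values are informative and differ by arm. This is plausible but not shown. The reasons that are arm-specific on their face, such as closed-loop-related events and suspend use in controls, are already invited. Baseline HbA1c and downloaded glucose data may explain part of the missingness.
- A reader might treat HbA1c as the leading secondary endpoint, or as the only outcome measurable after device use stops. The article gives it no such rank, and body weight, for one, can also be measured then.
- A reader might extend the point to questionnaires and conclude that acceptability is rated only by those who stay. The psychosocial methods section directs the feedback questionnaire to those randomised to closed loop, not to completers, and the withdrawal clause concerns HbA1c only.

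**Conclusion.** The point holds as a gap in planned data collection. Voluntary leavers after randomisation have no planned 12-week HbA1c, which weakens the intention-to-treat comparison for one secondary outcome tested at p<0.05. The text does not forbid asking them; it makes no provision for it.

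The size of any bias is unknown. Under the assumptions above it runs from zero (even split, equal gaps) to about 0.05–0.10 HbA1c points (four leavers in one arm of 42, gap 0.5–1.0). The count of reasons is firm; the link between leaving and arm is an inference from the open-label design. Neither the primary endpoint nor its sample size is affected. This is a cheap improvement to make, not a flaw that undermines the trial.

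**What to change.** Change the range from reasons 4–12 to reasons 3–12 for participants withdrawn after randomisation. Keep it a voluntary invitation, to give the central-laboratory HbA1c at the planned Visit 11 date, and exempt anyone who refuses further contact.

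The visit date and laboratory already exist. The cost is one changed number, matching consent wording and a few extra samples. Some of those invited will decline, so the gap will shrink but may not close.

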### Psychosocial methods

A mixed-methods psycho-social evaluation using in-depth interviews and validated questionnaires will be conducted to determine the utility of the device in terms of acceptability of intervention, quality of life, participants’ perception of impact on lifestyle and diabetes self-management.

Participants will be invited to complete the PedsQoL questionnaire at screening and at the end of the study intervention. In addition, a feedback questionnaire on closed-loop-specific experience will be distributed to participants/guardians who had been randomised to the closed-loop intervention arm.

A subset of participants (individuals aged 16+ years, individuals aged 13–15 years and their parent/guardian(s), parent/guardian(s) of participants aged 12 years and under) will be invited to take part in an interview at baseline (postrandomisation) to enable their historical diabetes management practices, everyday work/school and family lives and their initial understandings and expectations of using closed-loop technology to be captured and explored in depth. The same participants will be followed-up at the end of the study intervention to determine whether the use of the closed loop-matched expectations, whether any difficulties occurred, the benefits and downsides of using closed loop to support diabetes self-management for the duration of the trial and their views about how the technology might be improved.

A subset of partners/family members will be interviewed at 3 months to capture the benefits of using a closed-loop system from their perspectives, how this technology has impacted on their own lives and on their role in supporting diabetes management practices.

Recruitment to the interview study will continue until data saturation is achieved; that is, until no new findings are identified in new data collected. It is estimated that around 20–25 adults and youths with diabetes and 20 members will be interviewed. If necessary, participants will be purposely sampled to allow for diversity in the final sample in terms of age, gender, occupation/education and geographical location. Interviews will be digitally recorded with consent.

### HbA1c samples

Blood samples for the measurement of HbA1c levels will be taken at three different time points. At screening, HbA1c will be measured locally. HbA1c at the beginning and end of study intervention will be taken and measured at a central laboratory (University of Minnesota, Minneapolis, USA) using an International Federation of Clinical Chemistry and Laboratory Medicine aligned method.

### Statistical analysis

All analysis will be conducted on an intention-to-treat basis. Data from all randomised participants with or without protocol violation including dropouts and withdrawals will be included in the analysis. Data will not be truncated due to protocol deviations.

#### Primary endpoint

The primary analysis will evaluate between group difference in the time (midnight to midnight) spent in the target glucose range from 3.9 to 10.0 mmol/L (70–180 mg/dL) based on sensor glucose levels during the 12-week free-living phase.

A 5% significance level will be used to declare statistical significance for the primary outcome comparison.

Mean (SD) for % time spent in the target range will be tabulated by treatment group. A linear model will be used to compare the difference between the two intervention arms, while adjusting for baseline % time spent in the target glucose range and random site effect. A 95% CI will be reported for the difference between the treatment groups based on the linear model. Normality of the residuals will be assessed. If the residuals have highly skewed distribution, then ranked normal score transformation of outcome data will be applied in the regression model. However, previous experience suggests that % time in target glucose range will follow an approximately normal distribution. A detailed analysis plan will be provided separately.

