### Randomisation

Eligible subjects will be randomised using central randomisation software to the use of day-and-night closed-loop combined with pump suspend feature (threshold suspend) or to sensor-augmented insulin pump therapy. The randomisation will be stratified at each centre by the two age groups (equal proportion of youth (6–21 years) and adults (22 years and older)) and HbA1c groups (equal proportion of below and above 8.5% (69 mmol/mol)).

A subset of participants randomised to closed-loop will be invited to take part in an interview study led by an independent team of qualitative researchers at the University of Edinburgh. Participants will be interviewed before and/or at the end of the closed-loop study period.

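### The primary model omits two of the three randomisation strata (age group and HbA1c group); it stays valid, but is slightly conservative to the extent that these strata predict the outcome

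*Protocol article*

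**What the plan says.** The Randomisation section of the protocol article states that "The randomisation will be stratified at each centre by the two age groups" and, in the same sentence, by HbA1c below or above 8.5%. There are thus three stratification factors: centre, age group and HbA1c group.

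The Primary endpoint section compares the arms with a linear model "while adjusting for baseline % time spent in the target glucose range and random site effect". Neither age group nor HbA1c group is listed, and no reason is given. The section ends with "A detailed analysis plan will be provided separately".

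The Secondary endpoints section extends the approach: "Similar linear models as the primary outcome will be used to compare the between-treatment difference". The Psychosocial evaluation section does the same for the quality-of-life scores, each adjusted for its own baseline score.

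The Power calculation section assumes a "10%points improvement in time when glucose is in target glucose range with an SD of 14.5% points", from which it derives 76 evaluable patients. It plans to randomise 84 and mentions no covariate adjustment.

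**The concern.** Stratified randomisation balances age group and HbA1c group between the arms, so these factors contribute little to the true variability of the treatment estimate. A model that omits them leaves whatever they explain in the residual variance. The reported standard error can then exceed the true one: the confidence interval is wider than it need be and the test rejects less often than its nominal level under the null. The bias runs in the safe direction. What is at stake is precision that the design has already paid for, in the primary analysis and in the secondary models built on the same pattern.

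**Working it through.** **1. The plan's own figure.** Inputs from Power calculation: difference 10, SD 14.5, two-sided alpha 0.05, power 85%; 1:1 allocation is assumed.

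n per arm = 2 × (1.960 + 1.036)² × 14.5² / 10² = 37.8, rounded up to 38, so 76 in total. With 38 per arm, SE = 14.5 × √(2/38) = 3.33 and power = Φ(10/3.33 − 1.96) = 85.2%. The stated 76 reproduces without any gain from covariates.

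**2. Effect of omitting balanced strata.** Let r be the share of residual variance that age and HbA1c group explain beyond baseline time in range and site. The protocol does not give r, so a range is assumed. With strata balanced by design:

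- model SE / true SE = k = 1/√(1 − r)
- true alpha = 2 × (1 − Φ(1.96k))
- taking 14.5 as the residual SD without the strata, true SE = 3.33 × √(1 − r); power is Φ(10/true SE − 1.96k) with the strata omitted and Φ(10/true SE − 1.96) with them included.

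| Assumed r | SE overstated by | True alpha | Power, omitted | Power, included |
|---|---|---|---|---|
| 0 | 0% | 5.0% | 85.2% | 85.2% |
| 0.02 | 1.0% | 4.8% | 85.5% | 85.9% |
| 0.05 | 2.6% | 4.4% | 85.8% | 87.0% |
| 0.10 | 5.4% | 3.9% | 86.5% | 88.7% |

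If 14.5 were instead an SD already adjusted for the strata, omission would give 84.8%, 84.0% and 82.6% at r = 0.02, 0.05 and 0.10, against 85.2%. The protocol does not say that it is such an SD.

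**3. Simulation check.** Settings: 76 patients, four sites (assumed), blocks of four within site × age × HbA1c, site fitted as fixed, 5,000 runs per setting. At r = 0.10 with the strata omitted, under the null, the mean model SE was 3.35 against a true SD of 3.22, and type I error was 4.3%. Power was 83.3% omitted and 86.1% included. At r = 0 it was 82.5% and 82.3%, so including uninformative strata costs next to nothing. The direction agrees with the formulas. The power gap at r = 0.10 is a little larger than in the table, nearly 3 points.

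**4. What the document suggests about r for age.** Table 1 is the only source.

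- Control time in range: adults (63 + 57 + 66)/3 = 62; adolescents (53 + 48)/2 = 50.5; gap 11.5.
- Closed loop: adults (75 + 68 + 76)/3 = 73; adolescents (72 + 67)/2 = 69.5; gap 3.5.
- Average gap over two equal arms: (11.5 + 3.5)/2 = 7.5.
- With half the patients in each age group, share of variance before baseline adjustment: (7.5/2)² / 14.5² = 6.7%.

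Baseline time in range is already in the model. Take 11.5 as the baseline gap and assume a baseline slope of 0.3 to 0.6. The remaining gap is then 7.5 − 0.3 × 11.5 = 4.05 down to 7.5 − 0.6 × 11.5 = 0.6. The larger value gives (4.05/2)² / 14.5² = 2.0%. At r = 0.02 the table shows 85.9 − 85.5 = 0.4 power points. No comparable estimate can be made for HbA1c group or for the secondary outcomes.

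**The case against.** The strongest reply is that the harm is conditional and probably small. Baseline time in range is the same measure as the outcome and is likely to absorb much of what age and HbA1c group would predict. The HbA1c split also lies within an eligible range of only 7.5–10%. Table 1 compares different studies lasting 7 to 84 days, and its adolescents are not the 6–21 stratum. All of this stands, and it limits the size of the point.

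A reader might infer from the control column alone that age accounts for about 16% of the variance, (11.5/2)² / 14.5², and so expect a large loss. The documents do not support that. Half the patients receive closed loop, where the gap is 3.5 points, and the 16% takes no account of baseline adjustment.

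It can also be said that the secondary models are only described as similar and use each outcome's own baseline, that insulin dose is per kg, and that weight is analysed as a change. That is fair: nothing in the article measures how strongly age predicts these outcomes once those steps are taken. It does not supply the missing strata either.

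The last reply is that a separate analysis plan exists and may add them. The article therefore cannot show that the strata are finally excluded. But it names the covariates itself before it refers to that plan, so the stated list is open to comment as it stands.

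**Conclusion.** The omission is clear on the page: two of the three stratification factors are absent from a covariate list that the protocol fixes without explanation. The direction is also clear: the analysis is valid, and conservative to the extent that the strata remain prognostic. The size is not known. For an assumed partial R² of 0–10%, the standard error is overstated by 0–5%, true alpha is 5.0–3.9%, and about 0–2 power points are forgone at 76 patients. For age alone on the primary outcome, under the slopes assumed above, the figure is under 0.5 points.

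A reader might go further and conclude that the trial falls short of its planned 85% power. The documents do not support this. The 76 was derived without any covariate gain, and with 14.5 as the residual SD of the stated model, power without the strata is still at least 85.2% by the normal approximation. What is lost is a gain relative to a better-specified model. This is a low-cost improvement and does not threaten the trial's conclusions.

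**What to change.** Add age group (6–21 against 22 and older) and HbA1c as fixed effects to the primary linear model and to the linear models for the secondary outcomes, keeping the baseline value and random site. HbA1c may enter as the stratum used at randomisation or as screening HbA1c on a continuous scale. If the strata are to stay out, the plan should say why. Settle the choice before unblinded analysis, because covariates added later would look data-driven. The cost is a sentence in the protocol or analysis plan and two degrees of freedom; no new data are needed.
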